## Abstract

**Background:**

Postpartum hemorrhage (PPH) is associated with maternal morbidity and mortality and has an increasing incidence in high-resource countries, despite dissemination of guidelines, introduction of skills training, and correction for risk factors. Current guidelines advise the administration, as fluid resuscitation, of almost twice the amount of blood lost. This advice is not evidence-based and could potentially harm patients.

**Methods:**

All women attending the outpatient clinic who are eligible will be informed of the study; oral and written informed consent will be obtained. Where there is more than 500 ml blood loss and ongoing bleeding, patients will be randomized to care as usual, fluid resuscitation with 1.5–2 times the amount of blood loss or fluid resuscitation with 0.75–1.0 times the blood loss. Blood loss will be assessed by weighing all draping. A blood sample, for determining hemoglobin concentration, hematocrit, thrombocyte concentration, and conventional coagulation parameters will be taken at the start of the study, after 60 min, and 12–18 h after delivery. In a subgroup of women, additional thromboelastometric parameters will be obtained.

**Discussion:**

Our hypothesis is that massive fluid administration might lead to a progression of bleeding due to secondary coagulation disorders. In non-pregnant individuals with massive blood loss, restrictive fluid management has been shown to prevent a progression to dilution coagulopathy. These data, however, cannot be extrapolated to women in labor.

Our objective is to compare both resuscitation protocols in women with early, mild PPH (blood loss 500–750 ml) and ongoing bleeding, taking as primary outcome measure the progression to severe PPH (blood loss > 1000 ml).

**Trial registration:**

Netherlands Trial Register, NTR 3789. Registered on 11 January 2013.

**Electronic supplementary material:**

The online version of this article (10.1186/s13063-018-2512-z) contains supplementary material, which is available to authorized users.

## Background

Postpartum hemorrhage (PPH) is the main cause of maternal death worldwide and the main cause of severe maternal morbidity in the Netherlands and other high-resource countries. It is defined by the World Health Organization as blood loss more than 500 ml in the first 24 h after childbirth [1]. Annually in the Netherlands, more than 12,000 cases with more than 1000 ml of blood loss are reported; in about 750 cases, more than four units of packed cells, intensive care admittance or extensive surgical intervention is needed [2]. In total, 33.7% of all women in labor will have more than 500 ml blood loss, 5–13% [3, 4] of whom will experience blood loss of more than 1000 ml and an additional 24.3% of whom will have blood loss of 500 to 1000 ml [3].

Recent publications have shown an increasing trend in PPH in different high-resource countries over the past years [5]. This increase is not directly linked to an increase in women with risk factors for PPH. Two retrospective studies, performed in Australia and Canada, concluded that although the frequency of risk and protective factors for PPH changed during the study period, correction for these factors did not alter the increasing trends in PPH [6, 7].

This increasing trend in PPH is also observed in the Netherlands, despite the introduction of national measures to improve care for this population [4, 8].

Despite the implementation of guidelines, regular training, and obligatory courses, the incidence of PPH is still rising, which is all the more reason to evaluate currently advised protocols for managing PPH. Conclusive evidence for optimal hemostatic resuscitation in PPH is lacking [9]. The Managing Obstetric Emergencies and Trauma course and the Royal College of Obstetricians and Gynaecologists instructions advise generous volume resuscitation to restore blood volume and oxygen carrying capacity: about twice the lost volume and up to 3.5 l of fast fluid infusion in patients with unstable bleeding [10, 11]. The Dutch guidelines advise to start volume resuscitation when there is profuse blood loss; the specific amount is not quantified. This guideline is based on the same (animal) studies mentioned later in this protocol [12]. Volume resuscitation can be done with crystalloids, colloids, or red blood cells in different volume strategies, which all have advantages and disadvantages (see the discussion for a more detailed outline). Our hypothesis is that massive fluid administration might lead to a progression of bleeding due to secondary coagulation disorders in women with PPH.

## Methods and design

### Aims

The aim of the Restrictive Versus Massive Fluid Resuscitation Strategy (REFILL) study is to determine whether in women with early, mild PPH (blood loss 500–750 ml) and ongoing blood loss, restrictive fluid resuscitation strategy reduces progression to severe PPH (defined as blood loss > 1000 ml) compared with care as usual. We hypothesize that restrictive fluid resuscitation will lead to a decrease in progression to severe PPH and therefore a decrease in its adverse outcomes.

### Participant’s criteria and recruitment

In this multicenter study, women with 500–750 ml blood loss postpartum and ongoing bleeding will be eligible for the study. The study will be performed in three Dutch hospitals, two university hospitals (Maastricht University Medical Center, Radboud University Medical Center) and one regional teaching hospital (Zuyderland Medical Center). The Maastricht Medical Center is the coordinating center.

All women attending the outpatient clinic or admitted to the ward and not in active labor who meet the inclusion criteria (see further) will be informed about the study by the treating physician or research nurse. Oral and written informed consent will be obtained. When women present at the labor ward, they will be asked to confirm orally whether they still want to participate in the study (see Fig. 1).

**Fig. 1 Fig1:**
[figure not shown]
SPIRIT flow diagram. **t*_1_ at 500–750 cm^3^, resuscitation within randomized protocol starts, blood withdrawal. ***t*_2_, 45–60 min after *t*_1_, second blood withdrawal. ****t*_3_ 12–18 h after *t*_1_, third blood withdrawal. **** i.e. maternal age, ethnic background, parity (nulliparous or multiparous), gestational age, obstetric history, length, weight, use of oxytocin, mode of delivery (vaginal delivery, instrumental delivery, or Cesarean section), delivery of placenta (spontaneous or manual), life birth, and birth weight. ***** All different treatments to resolve the underlying cause of PPH given to the patient will be registered, intensive care admittance, the need of four or more units of packed cells, embolization, and hysterectomy, laboratory results at *t*_1_, *t*_2_, and *t*_3_

Inclusion criteria are:Pregnant and labor starting after 24 + 0 weeksAge ≥ 18 years

### Informed consent

Mentally competent, understanding Dutch language

Exclusion criteria are:Prophylactic or therapeutic anticoagulant therapy (carbasalate calcium within the previous 10 days or low molecular weight heparins within previous 48 h)Known congenital coagulation disordersPre-eclampsia (higher risk of low plasma volume, higher risk of volume overload)Antenatal diagnosis of placenta accreta, increta, or percretaContraindication for massive fluid therapy (e.g. cardiac causes, systemic causes (Marfan), renal causes, pulmonary failure)

### Randomization, procedures, and collection of data

In women with more than 500 ml blood loss and ongoing blood loss, randomization takes place. Treatment allocation is blinded by use of opaque and sealed envelopes. The randomization is stratified per center, in blocks of four and concealed, in an allocation of 1:1. The envelopes will be distributed per center by Maastricht University Medical Center. The required randomization envelopes will be quickly and easily accessible at the labor ward. Participants will be randomized to either the intervention group (receiving fluids at 0.75–1.0 times the blood loss) or the control group, who will receive care as usual (receiving fluids at 1.5–2.0× blood loss).

In women participating in the study, blood loss will be measured by weighing the absorption towels after childbirth, excluding the first one directly after giving birth, as this will include amniotic fluid. In current care, generous volume resuscitation is standard; this consists of about twice the lost volume and 2 l fast infusion in patients with unstable bleeding. Volume resuscitation will primarily be done with a fast infusion of crystalloids or Ringers lactate. In all women, the first 2000 ml will consist of a fast infusion of NaCl (0.9%) or Ringers lactate, or a combination of the two.

At the stage of 500–750 ml blood loss, the study protocol starts (*t*_1_). Intravenous access will be established and a blood sample taken for testing hemoglobin concentration, hematocrit, platelet count, activated partial thromboplastin time, prothrombin time, and fibrinogen concentration. Women delivering in the Maastricht University Medical Centre ROTEM® analysis (FIBTEM, APTEM, INTEM, EXTEM) will be included. Hemodynamic parameters include blood pressure and oxygen saturation, as measured using continuous pulse oximetry.

Additional clinical parameters will guide management and serve as a safety check. We aim to maintain systolic blood pressure > 90 mmHg and diastolic blood pressure > 50 mmHg, or a decrease of less than 20 mmHg. The maternal heart rate should be less than 125 beats per minute [13]. If these cut-off values are crossed, an additional volume of 500 ml will be administered in 15 min, in both groups.

At *t*_2_, 45–60 min after the initial start of infusion, two situations can occur:The patient is stable, defined as normal ongoing blood loss (< 1 full sanitary pad/h) with stable blood pressure and pulse. At this point, we will take an extra blood sample, to test for hemoglobin concentration, hematocrit, platelets, activated partial thromboplastin time, prothrombin time, and fibrinogen concentration.The patient is still bleeding, defined as > 100 ml/h. If the blood loss is greater than one full sanitary pad per hour, the blood loss will be weighed again. Laboratory tests for hemoglobin concentration, hematocrit, and coagulation status will be done, as part of regular care.

At *t*_3_, 12–18 h postpartum, the last blood sample will be taken for hemoglobin concentration and hematocrit analysis. This is part of regular care in women with blood loss > 500 ml.

In the case of > 1500 ml blood loss, the study protocol will be terminated and patients will be treated according to local massive hemorrhage protocol. Blood samples will still be drawn and the patient will be analyzed on an intention-to-treat basis.

Except for the fluid resuscitation, treatment of the underlying cause of the PPH will be according to the local and national protocol (Nederlandse Vereniging voor Obstetrie en Gynaecologie (NVOG) guidelines) in both groups, which will be noted in the clinical chart and registered in the trial data. We expect this to be similar in both groups. The NVOG guidelines advise basal preventive measures to identify women at high risk, consisting of: an active third stage of labor consisting of pre-labor use of an intravenous access and recently known and matched blood type, weighing the amount of blood loss when the blood loss seems profuse and a preventive administration of 5 IU of oxytocin intravenously after childbirth and before placental birth. In women at high risk of PPH, an additional 10 IU oxytocin is administered in a course of 4 h postpartum. The guidelines do yet not recommend tranexamic acid in a preventive setting. If oxytocin is ineffective, or only partially effective, sulprostone (500 μg in 30 min followed by 60–120 μg/h) or methylergometrine (0.2 mg intravenously or intramuscular) is recommended. If blood loss is more than 1000 ml or if more than 2000 ml crystalloids are given, the guidelines advise blood testing (activated partial thromboplastin time, prothrombin time, thrombocyte concentration, fibrinogen concentration, or thromboelastometry, if available) and correct deficiencies accordingly. In expectation of the laboratory results, fibrinogen or tranexamic acid may be administered. This recommendation dates from after the start of the study.

Other study parameters regarding obstetric history and the current pregnancy will be collected from the patient’s chart.

All data are collected and stored anonymously in Maastricht Medical Center in a restricted access file. A trial number assigned to each patient will be used in the dataset to ensure anonymous data collection. These trial numbers are stored securely and locked from the dataset. Data will be imputed as soon as possible after study participation. The dataset will be saved; data will be marked separately by date of saving. Data will be stored for 15 years. PS, NL, HS, and LS will have access to final dataset.

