A retrospective analysis by Duke *et al.* [27] of trauma patients showed an overall lower mortality rate, lower intraoperative mortality, and a shorter hospital stay in the restrictive resuscitation group. Despite the fact that the groups were well-matched, the retrospective character of the study is a limitation and bias cannot be ruled out [27].

A prospective randomized pilot trial comparing controlled resuscitation versus standard resuscitation in hypotensive trauma patients demonstrated that controlled resuscitation strategy can be successfully and safely implemented in a civilian environment. The results showed a reduction of early crystalloid resuscitation volume, but also an increase in early blood product transfusion [28].

In all, these studies, there were difficulties in following the study protocol strictly. This may be explained by the fact that these studies were performed in an acute setting and by the impossibility of blinding the treating clinicians, who might be less familiar with restrictive resuscitation.

In conclusion, there is little and contradictive evidence for either aggressive or restrictive fluid resuscitation, and it is very difficult to perform good clinical trials. This is reflected in the latest guidelines. The European Society of Anaesthesiology guidelines on management of severe perioperative bleeding recommend avoidance of hypervolemia. Permissive hypotension is not mentioned, but implementation of delayed or low-volume resuscitation protocols is not yet recommended [29]. Conversely, the updated European guidelines on management of bleeding and coagulopathy following major trauma recommend a target systolic blood pressure of 80 to 90 mmHg until major bleeding has been stopped in the initial phase following trauma without brain injury [30].

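### A single fixed block of four per center, with visible arms and envelopes on the ward, lets anyone who follows the sequence foresee up to one allocation in three

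*Protocol article*

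**What the plan says.** All of the allocation procedure stands in the protocol article, section *Randomization, procedures, and collection of data*.

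- Sequence: "The randomization is stratified per center, in blocks of four and concealed, in an allocation of 1:1". Only one block size is given.
- Concealment: "Treatment allocation is blinded by use of opaque and sealed envelopes". The word blinded here describes concealment of the next allocation; no masking of the infused fluid is described.
- Supply and storage: "The envelopes will be distributed per center by Maastricht University Medical Center", and "The required randomization envelopes will be quickly and easily accessible at the labor ward".
- Arms: fluids at 0.75–1.0 times the blood loss, against "the control group, who will receive care as usual" at 1.5–2.0 times the blood loss.
- Trigger: "In women with more than 500 ml blood loss and ongoing blood loss, randomization takes place". The section *Participant’s criteria and recruitment* gives the range: women with 500–750 ml "blood loss postpartum and ongoing bleeding will be eligible for the study".

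The same recruitment section names three hospitals and places consent before active labor. *Trial status* reports 179 of 250 women enrolled, with recruitment continuing.

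**The concern.** Sealed opaque envelopes hide the next card. They cannot hide a card that the previous cards already imply. With one constant block size, each block ends in at least one allocation that follows from those before it. Each used allocation is visible to the staff who run the infusion, and each of the three centers has its own short sequence.

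Foreknowledge matters only if someone can act on it. Two things at entry are left to judgment: whether bleeding is ongoing, and when within a 250 ml window (750 − 500) the envelope is opened. The >100 ml/h definition of continued bleeding is given for the second time point, not for entry.

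The window bears on the primary outcome, blood loss above 1000 ml. A woman entered at 500 ml has 500 ml to go before she counts as an event; one entered at 750 ml has 250 ml to go. If the timing of entry, or the choice of who is entered, depended on the foreseen arm, baseline risk could differ between the arms.

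**Working it through.** **Inputs.** Block size 4, ratio 1:1, stratified by center (*Randomization*). Three centers (*Participant’s criteria and recruitment*). Target 250; planned event rates 30% and 15% (*Sample size calculation*). Enrolled 179 (*Trial status*).

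**The plan's own figure.** The article gives no predictability figure to reproduce. Its sample size does reproduce: with unpooled variance and two-sided alpha 0.05, (1.960 + 0.842)² × (0.30 × 0.70 + 0.15 × 0.85) / 0.15² gives 118 per arm after rounding up. This point does not alter that number.

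**Share of allocations that are certain.** A 1:1 block of four has 6 equally likely orders. An allocation is certain once one arm is used up within the block.

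| Position in block | Probability that the allocation is certain | Probability that the best guess is right |
|---|---|---|
| 1 | 0 | 1/2 |
| 2 | 0 | 2/3 |
| 3 | 2/6 = 1/3 (first two match) | 1/3 × 1 + 2/3 × 1/2 = 2/3 |
| 4 | 1 | 1 |
| Mean | (1/3 + 1)/4 = 1/3 | (1/2 + 2/3 + 2/3 + 1)/4 = 17/24 = 70.8% |

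The 1/3 is exact for completed blocks and assumes a fully informed guesser.

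**Women still to be enrolled.** 250 − 179 = 71, and 71/3 = 23.7, so up to about 24 allocations.

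**Effect of varied blocks.** This was simulated with block sizes drawn at random with equal probability. The guesser knows the set of sizes, every past allocation and where the sequence began, but not the order of the sizes. About 24 women per center is an even split of the 71 (assumption); 83 per center is an even split of 250.

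| Scheme | Certain, 24 per center | Best guess, 24 per center | Certain, 83 per center | Best guess, 83 per center |
|---|---|---|---|---|
| Blocks of 4 and 6 | 5.8% | 68.6% | 5.5% | 69.0% |
| Blocks of 4, 6 and 8 | 2.4% | 67.3% | 2.4% | 67.8% |

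With blocks of 4, 6 and 8, about 71 × 0.024 = 1.7 allocations would be certain, instead of up to about 24.

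**What it could do to the result (illustration; the shift is assumed).** Suppose every foreseeable slot among the last 71 were filled by a woman whose risk differs by d points in a direction that depends on the foreseen arm. In each arm, 1/3 of the women enrolled in this period shift by d, so the arm difference shifts by 2d/3 among the 71, or by (71/250) × 2d/3 = 0.19d overall. For d = 5 to 10 points that is about 0.9 to 1.9 points, against a planned difference of 15. This requires perfect tracking and consistent steering.

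**The case against.** The strongest reply is that predictability in principle is not predictability on this ward. Certainty needs someone who knows the block size, where the block began and every earlier allocation in it. Accrual was slow. From August 2014 to October 2017 is 38 months, and the count of 179 dates from then or later, so the rate was at most about 179/38 = 4.7 a month. That is about 1.6 per center per month if evenly spread (assumption), so a block would span about 4/1.6 = 2.5 months. Staff would have to follow colleagues' patients over that time and use the knowledge in an emergency. In addition, consent precedes labor and blood loss is weighed. This stands as a reason to call the figures upper limits. It does not remove the weakness: a faster center shortens the span, and three short sequences with visible arms can be followed.

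A reader might infer four stronger things that the article does not support.

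- *One third of all 250 allocations, about 83, were known in advance.* Publication can bear only on the last 71 women. Whether sites knew the block size before is not shown.
- *Staff knew the block size and the favorable interim message and acted on both.* Both are printed in the article. That ward staff read or used them is not shown, and the interim disclosure is a separate matter.
- *The authors declare this trial unblinded.* Visibility of the arms is inferred from the intervention. The remark on "the impossibility of blinding the treating clinicians, who might be less familiar with restrictive resuscitation" concerns earlier trauma trials.
- *Envelope numbering, custody and opening times are not recorded.* An article commonly leaves these to the full protocol, so their absence here shows nothing.

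**Conclusion.** The point holds as a conditional weakness in a stated design choice. One fixed block size per center, visible arms and envelopes on the ward weaken the concealment that the article claims. An informed observer could foresee up to one allocation in three, which is up to about 24 of the 71 women outstanding at publication. This assumes knowledge of the block size and complete tracking of the current block; neither is shown to have occurred. Entry is only partly a matter of judgment, so the room for selection is limited but real. There is no evidence of bias in the women already enrolled, and the sample size is unaffected. This is a cheap improvement, not a flaw that invalidates the comparison.

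**What to change.** For the women still to be randomized, replace the unused envelopes at each center with a new sequence of randomly varied block sizes, for example 4, 6 and 8, still 1:1 and stratified by center. Do not disclose the order of the sizes to the sites.

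Moving the remaining allocations to central web or telephone release would not cure this by itself, because a fixed block of four stays predictable however it is released. It would also have to be weighed against the article's stated need for rapid access on the ward.

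Costs and limits:

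- a small protocol amendment during recruitment, and reprinting of the remaining envelopes;
- slightly larger possible imbalance within a center: the largest gap inside an unfinished block is half its size, so 4 with a block of 8 against 2 with a block of 4;
- only a modest fall in best-guess accuracy, from 71% to about 67–68%, so the gain lies in removing certainty;
- no protection for the 179 women already randomized.

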### Outcome measures

#### Primary objective

The primary objective is to establish whether in women with early, mild PPH (blood loss 500–750 ml) a fluid resuscitation strategy with fluids 0.75–1.0 times the blood loss reduces the progression to severe PPH (defined as blood loss > 1000 ml), compared with fluid resuscitation with fluids 1.5–2.0 times the blood loss.

#### Secondary objective

Secondary outcomes are: difference in hemoglobin concentration (mmol/l) 12–18 h postpartum (including differences in hemoglobin < 5.0 mmol/l), differences in transfusion requirements (defined as the number of units of packed red blood cells, fresh frozen plasma, thrombocytes, and fibrinogen needed), differences in the amount of coagulopathies, defined as individually abnormal laboratory results according to current treatment protocols (meaning platelets < 50 × 10,9 fibrinogen concentration < 1 g/L and activated partial thromboplastin time and prothrombin time > 1.5 × mean control).

Severe adverse outcomes will be registered. We define serious adverse outcomes as intensive care admittance, the need of four or more units of packed cells, embolization, and hysterectomy [2].

